## Background

Radiotherapy has a significant role to play in the management of cancers of the upper abdomen, but high dose radiotherapy has been considerably limited by potential adverse normal tissue responses, in particular that of the kidneys. Because of their proximity to organs such as the pancreas, stomach and oesophagus, incidental radiation dose to the kidneys is frequently unavoidable when planning radiotherapy treatment. Our current understanding of kidney dose response and tolerance to radiation is rudimentary. This limits the delivery of a higher dose to the tumour and also the introduction and optimisation of new techniques to treat these upper gastrointestinal cancers, such as intensity modulated radiation therapy (IMRT).

Until recently, estimation of radiation-induced kidney damage was based on analysis of very basic radiotherapy data by Emami et al [1]. The Quantitative Analyses of Normal Tissue Effects in the Clinic (QUANTEC) review collated results of relevant studies that have been undertaken so far [2]. There have been previous key studies that have addressed the effects of partial kidney irradiation. In 1973, Thompson et al [3] reported the occurrence of clinical kidney toxicity several years after radiotherapy. Willet et al [4] found a dependence on the percentage of the volume being irradiated with a decrease in creatinine clearance. More recently, Kost et al [5] in 2002, used sequential scintigraphy to assess impairment of renal function and correlated it with the radiation dose distribution. Jansen et al [6] observed a progressive decrease in renal function in gastric cancer patients after postoperative radiotherapy. Studies in pigs [7,8] have shown that the response is dependent on whether one or both kidneys are irradiated and that the functional response depends on the compensatory response of the non-irradiated kidney.

A review of the preceding studies and the QUANTEC report [2] has highlighted several key points which have influenced the design of the RAPRASI study protocol:

– Kidneys have a late response to radiation (between 3 and 18 months).

– The functional response is dependent on the percentage of the kidney volume being irradiated and the dual nature of this organ influences their response.

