### Study hypotheses

An assessment of changes in total kidney function (using GFR measurement), regional kidney functional change (using SPECT imaging) and their correlation with radiotherapy dose delivery is within the means of currently available imaging, therapy and computational technology. The hypotheses being tested in RAPRASI are:

– Temporal variations in SPECT images of the kidneys correlate with patterns of radiation dose delivery in the kidneys.

– Models of kidney response developed from SPECT-response studies can be used to predict changes in kidney function as a result of radiation therapy.

The principal aim of RAPRASI is to obtain a better understating of kidney response when a patient is receiving radiotherapy for an upper-abdominal cancer. This will involve monitoring the spatial and temporal changes in kidney function for correlation with delivered three-dimensional radiation dose distribution. A more precise dose-volume response model for kidney will not only improve our current understanding but may permit further optimisation of radiation therapy techniques for upper-abdominal tumours.

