### Inclusion criteria

– Males or females older than 18 years of age.

– Histologically/cytologically proven upper GI adenocarcinoma.

– Signed written informed consent provided to participate in the study.

– Radical radiotherapy (dose > 40 Gy in 4 weeks) being prescribed to an upper abdominal site that will involve incidental radiation of one or both kidneys.

– Loco regional staging of primary disease will have been undertaken with dual phase (arterial and portal) spiral CT.

– Serum creatinine ≤150 *μmol/L.*

– Performance status is ECOG grade 0, 1 or 2 [17].

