### Data collection and quality assurance

This study will be conducted according to the Human Research Ethics Committee (HREC)-approved study protocol and the ‘Note for Guidance on Good Clinical Practice (CPMP/ICH/135/95) annotated with TGA comments’ (Therapeutic Goods Administration DSEB July [18]. The study will be performed in accordance with the NHMRC ‘National Statement on Ethical Conduct in Human Research’ (© Commonwealth of Australia 2007) and the ethical principles within the ‘Declaration of Helsinki’ (Revised 1996) [19].

Sir Charles Gairdner Hospital will act as the sponsor of this study at both the Peter MacCallum Cancer Centre and Sir Charles Gairdner Hospital in Perth, Western Australia. Standard medical care (prophylactic, diagnostic and therapeutic procedures) remains the responsibility of the patient’s treating physician.

The investigator is responsible for ensuring that no participant undergoes any study related examination or investigations prior to obtaining written informed consent. The investigator will explain the aims, methods, possible benefits and potential hazards before the participant gives consent. The participant will be given sufficient time to read the documentation, understand the project and have any questions addressed prior to signing the consent form. The participants will be advised that they have the right to withdraw their consent to participate at any time without any consequences.

Participant confidentiality will be protected at all times. In any resulting publication or presentation, no patients will be identified.

Records will be retained for 15 years post study completion in a locked facility, in accordance with TGA requirements. Access to participant study records will be limited to treating clinician, chief investigator, his/her nominated co-investigators and the local study co-ordinators.

Collation of data will yield the following for each participant:

– Local kidney function/response to therapy: regional change in SPECT signal intensity:

•from baseline to 4 weeks post start of radiotherapy

•from baseline to 12 weeks post start of radiotherapy

•from baseline to 26 weeks post start of radiotherapy

•from baseline to 52 weeks post start of radiotherapy

•from baseline to 78 weeks post start of radiotherapy

– Planned 3D Regional radiation dose distributions intended to be experienced during radiation treatment.

– Kidney function measure: GFR at baseline, 4, 12, 26, 52 and 78 weeks.

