It is anticipated that all participant data will be utilized in the final analysis provided that each participant completes at least the baseline (pre-radiotherapy) and first SPECT/CT scan at 4 weeks post start of radiotherapy. If a participant commences radiotherapy (i.e. completes the baseline SPECT/CT scan) but withdraws consent mid-treatment or is unable to complete any further SPECT/CT scans, then the data for that participant will be excluded from the final analysis.

Data relating to co-morbidities and concurrent treatments, including adjuvant chemotherapy, known to influence kidney toxicity [2], will be extracted from participant notes.

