**Figure 2 F2:**
[figure not shown]
Diagram of the co-registration method.

This subsequent analysis of co-registered dose and image data will be undertaken in several ways:

i. Methods will be developed to assess dose-response correlations as a function of spatial position across each kidney (sampled at varying resolutions). Kidney volumes will be uniformly divided into regions on the three-dimensional (3D) grid defining image and spatially-registered radiation dose. t-tests and Wilcoxon signed-rank tests will be undertaken to determine regions with significantly different mean SPECT-signal intensities between time-points for each study participant. Mixed modelling with repeated measures (and random subject effect) will be conducted across all participant sets to examine the correlation of local radiation dose with SPECT signal changes, generating a map of dose-response change across all kidney volumes. Given a significant correlation, this will be extended to incorporate any revealed patterns of co-morbidity or adjuvant therapy as categorical variables.

ii. Dose-response correlations will then be examined according to structural and functional regions. Analysis i. will be repeated, but with regions defined according to kidney structure, with medulla, renal artery and cortex regions treated independently. This will also involve cross-correlation between these regions to examine inter-play that is likely to arise due to the influence of radiation effects on vascular structures.

iii. Spatio-temporal mathematical models of functional kidney dose-response will be implemented to relate regional kidney irradiation to the primary measure of total kidney function, GFR. These models, including percolation theory [25] and the critical functioning volume model of Rutkowska et al [26], will utilise the 3D radiotherapy dose distribution (both across each kidney and across individual functional regions) to fit model parameters using maximum likelihood estimation (MLE) methods. The statistical assessment of fitting will be made by assessment of parameter confidence intervals, and by undertaking an F-test of the residual sums-of-squares from MLE against that from MLE for a simple linear (single-parameter) dose-response model.

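### In analysis iii the F-test sets spatio-temporal GFR models against a dose slope with no time or dose-independent term, so a significant result alone cannot support the spatial or volume description

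*Protocol article*

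**What the plan says.** Under Data analysis, analysis iii of the protocol article, "Spatio-temporal mathematical models of functional kidney dose-response will be implemented to relate regional kidney irradiation to the primary measure of total kidney function, GFR". The candidates named are percolation theory and a critical functioning volume model, which "will utilise the 3D radiotherapy dose distribution (both across each kidney and across individual functional regions) to fit model parameters using maximum likelihood estimation (MLE)". Fit is judged in two ways: by confidence intervals for the parameters, and by "undertaking an F-test of the residual sums-of-squares from MLE against that from MLE for a simple linear (single-parameter) dose-response model".

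Four other statements bear on this reference:
- Background: "Kidneys have a late response to radiation (between 3 and 18 months").
- Data collection and quality assurance: "Kidney function measure: GFR at baseline, 4, 12, 26, 52 and 78 weeks".
- Inclusion criteria: radical radiotherapy "being prescribed to an upper abdominal site that will involve incidental radiation of one or both kidneys". Every patient therefore has some kidney dose, and there is no unirradiated group.
- Data collection and quality assurance: "Data relating to co-morbidities and concurrent treatments, including adjuvant chemotherapy, known to influence kidney toxicity" are to be extracted from the notes. Co-morbidity and adjuvant therapy are planned as model terms in the SPECT mixed model (analysis i, repeated in ii). None is stated for the GFR models of analysis iii.

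The second study hypothesis is that "Models of kidney response developed from SPECT-response studies can be used to predict changes in kidney function as a result of radiation therapy".

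**The concern.** A linear dose-response model with a single parameter says that GFR change is proportional to dose and the same at every visit. The protocol already expects that to be untrue: it describes a response developing over months and measures GFR from 4 to 78 weeks. It also recognises causes of renal toxicity other than dose.

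The rival can beat this reference in three ways. Its spatial or volume description may be right, it may simply contain time, or it may absorb a fall that has nothing to do with dose. The F-test does not tell these apart. At stake is the reading of the result: a significant test would naturally be reported as support for a percolation or critical-volume model over a simple dose model, and a more precise dose-volume model is what the study's principal aim is meant to deliver.

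**Working it through.** **The plan's own figure.** There is none for this test. The stated 33 patients (10% reduction, 20% error, 80% power) belong to the SPECT paired t-test. The normal approximation gives (1.960 + 0.842)² × (20/10)² = 31.4 and the exact t gives 34, so that figure is roughly reproduced, but it does not bear on the F-test.

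**Inputs from the article.** 30 datasets; follow-up at 4, 12, 26, 52 and 78 weeks; one-parameter reference. The 5% level is borrowed from the SPECT calculation.

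**Assumptions.** Visits pooled (150 values); mean kidney dose D uniform on 3–20 Gy; independent normal errors with SD σ; outcome is percent change in GFR; true dose effect zero; common drift −Δτ with τ = week/78. Reference: b·D. Stand-in nested rival: b·D + c·D·τ, giving 1 and 148 degrees of freedom and a critical value of 3.905.

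**Closed form.** D·(τ − τ̄) is orthogonal to D, so projecting the drift on it gives the noncentrality

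λ = N·Δ²·(D̄²/E[D²])·S/σ², with S = Σ(τ − τ̄)².

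- τ = 0.051, 0.154, 0.333, 0.667, 1; τ̄ = 0.441; S = 0.609.
- D̄ = 11.5; variance = 17²/12 = 24.08; E[D²] = 132.25 + 24.08 = 156.33; ratio = 0.846.
- Δ = 10, σ = 10: λ = 30 × 100 × 0.846 × 0.609/100 = 15.5, rejection 97%.
- Δ = 10, σ = 20: λ = 15.46/4 = 3.87, rejection 50%.

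Simulation agrees. Rejection rates with no dose effect:

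| Drift by week 78 | Planned reference, σ = 10 | Planned reference, σ = 20 | Visit means in both models, σ = 10 |
|---|---|---|---|
| 0% | 5% | 5% | 5.5% |
| 2% | 12% | – | 5.8% |
| 5% | 51% | 18% | 5.0% |
| 10% | 97% | 50% | 5.4% |
| 20% | 100% | 97% | 5.1% |

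With doses of 4–20 Gy and 10% drift, the planned test rejects in 97%, 76% and 53% at σ = 10, 15 and 20.

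**Other rivals.** A four-parameter saturating dose curve multiplied by an onset term rejects in 0.5%, 33%, 97% and 100% at drifts of 0, 5, 10 and 20% (σ = 10), and in 0.7%, 3.5%, 33% and 98% at σ = 20.

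**Correlated visits.** With an added patient-level SD of 10 and σ = 10, the simple rival rejects in 0.8%, 21% and 86% at drifts of 0, 5 and 10%.

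**Week 78 alone.** Time drops out, but the reference still has no intercept. At 10% drift and σ = 10, a quadratic-dose rival rejects in 44%. The saturating rival rejects in 33% for doses of 3–20 Gy and 2% for 8–18 Gy. Adding an intercept brings the saturating rival below 1%, but the reference is then no longer single-parameter.

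**Response exactly linear in dose but growing to 10% at week 78** (doses 4–20 Gy): the planned test rejects in 99%, 86% and 62% at σ = 10, 15 and 20. A linear reference with the same time function returns this to 4–6%.

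**The case against.** Five points can fairly be made on the other side.

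1. **The F-test is not the only criterion.** Parameter confidence intervals stand beside it. With the rival b·D^n·τ^p, no dose effect and 10% drift, the F-test rejects in 99.7%, 83% and 56% (σ = 10, 15, 20). Yet it rejects with n also significantly above zero in only 0.7%, 0.7% and 0%. This stands for that rival. It does not carry over to b·D + c·D·τ: there the one-degree-of-freedom F-test is the square of the t-test for c, so the interval for c excludes zero exactly when the F-test rejects.

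2. **Rejection in the linear-but-growing case is correct.** A reader might count those 62–99% as false positives. They are not: a model with time really does fit better than one without, and the study aims to describe temporal change. The result misleads only if taken as evidence for a volume or architecture description.

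3. **The article does not call this F-test the test of its second hypothesis.** It calls it an assessment of fitting. Prediction is to be examined by fitting on the first 20 patients and predicting the next 10. That stands, but the hold-out is stated for SPECT signal changes, not GFR.

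4. **The candidate equations, pooling of visits, drift and SD are not given.** A reader might infer that the test will reject whenever GFR changes over time. The documents do not support that: the saturating rival stays at 3.5% with 5% drift and σ = 20.

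5. **Eligibility limits drift.** The design calls for stable renal function, caps serum creatinine and excludes nephrotoxic treatment. This reduces dose-independent loss, but the article itself still expects co-morbidity and chemotherapy to matter.

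Detail left to a fuller document would be no finding. Here, however, the article positively fixes the reference as single-parameter.

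**Conclusion.** The point holds in a limited form. The reference stated in analysis iii has no fitted time or dose-independent term, so a significant F-test may reflect time course or drift and cannot by itself support the spatial or volume description. With pooled visits, 30 patients, no dose effect and a common 10% drift by week 78, a simple nested rival containing time rejects in roughly 50–97% of trials at residual SDs of 20 down to 10 points. Drift, SD, dose range, pooling and the form of the rival are all assumptions. Smaller drift or a different rival can bring the rate close to or below the nominal 5%.

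It does not follow that the plan has no means of supporting a dose-volume claim. The confidence intervals may guard against the misreading for some models, though not for all, and the SPECT analyses are unaffected. The change is worth making because the reference is a stated rule and the remedy needs no new data.

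**What to change.** In analysis iii, give the reference and the spatio-temporal model the same dose-independent visit terms. Where the models are nested, report F-tests against two references:

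- (a) visit terms only, to show that dose predicts GFR change;
- (b) visit terms plus linear mean kidney dose acting through the same time function, to show that the volume or architecture description adds to the fit.

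Claim support for the dose-volume description only from (b).

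Matched terms do not deal with correlation between a patient's own visits. With a patient-level SD of 10 and σ = 10, a pooled test of a quadratic dose term still rejected in 26–29% despite visit means in both models. The random subject effect already planned in analysis i should therefore be carried over, with a comparison suited to it.

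The cost is analysis wording and two extra reference fits on data already being collected. The downside is a few more reference parameters and weaker-looking evidence for the complex models.

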iv. An export of co registered dose and SPECT information will be made for regions defined by whole kidneys, separately-identified medulla and cortex, baseline-image functional regions, and at varying spatial resolutions. Renal response patterns obtained from variations in SPECT and GFR shall be fitted to normal-tissue complication probability (NTCP) and equivalent uniform-dose (EUD) models, as previously undertaken by CI’s using estimated parameters [27,28]. Response indicators can be related to dose volume histogram (DVH) and dose-function histogram (DFH) data by maximum likelihood fitting to the parametric NTCP/EUD models. For this purpose, the freely available DREES code [29], developed in Matlab, will be utilised. Separate analyses will be undertaken using acute changes in SPECT signal (< 12 week images) as well as the long-term changes indicated by images taken at 52 or 78 weeks post-radiotherapy.

Examination of the predictive nature of response models will be made by establishing parameters based on the first 20 patient data sets, and utilising the models to predict SPECT signal changes on the subsequent 10 patients. In order to minimise parameter uncertainties however, final parameter values will be based on data for all patients.

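### The F-test comparing the GFR models with a one-parameter line is valid only for nested models and independent residuals, and the article establishes neither

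*Protocol article*

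**What the plan says.** Item iii of the Data analysis section (Protocol article, after Figure 2) fits mathematical models to "relate regional kidney irradiation to the primary measure of total kidney function, GFR". The list of models is open: "These models, including percolation theory [25] and the critical functioning volume model" are given as examples, without equations or parameter counts. The data are used "to fit model parameters using maximum likelihood estimation (MLE) methods".

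Two criteria of fit follow in one sentence. The first: "The statistical assessment of fitting will be made by assessment of parameter confidence intervals". The second is "an F-test of the residual sums-of-squares from MLE against that from MLE for a simple linear (single-parameter) dose-response model".

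Three other statements bear on this:

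- The Data collection section lists the outcome as repeated: "Kidney function measure: GFR at baseline, 4, 12, 26, 52 and 78 weeks". That is one baseline and five follow-up values per patient.
- Item i of the same section uses a repeated-measures mixed model with a random effect for subject. Item iii mentions no such term.
- A separate predictive check consists of "establishing parameters based on the first 20 patient data sets, and utilising the models to predict SPECT signal changes on the subsequent 10 patients". Its target is SPECT signal, not GFR.

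**The concern.** The extra-sum-of-squares F-test compares the fall in residual sum of squares, per added parameter, with the residual variance of the larger model. The ratio follows an F distribution when the smaller model is a restriction of the larger one and the errors are independent with equal variance. If the models are not nested, the larger one need not fit better, so the numerator can be negative, and the tabulated F distribution is no longer the right reference. Reading the test as a plain ratio of two residual variances does not help, because both come from the same GFR values and are not independent.

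Nothing in the article says that a straight line in dose is contained in the models named. Models built on connectivity, or on a functioning volume crossing a critical level, would not normally contain one. Independence is also open: the models are described as spatio-temporal, which suggests that several visits per patient enter the fit, and no within-patient term is named.

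At stake is the only stated comparison of the GFR models with a simple alternative. Confidence intervals describe how precisely parameters are estimated. They do not say whether a mechanistic model does better than a line.

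**Working it through.** **The plan's own figure.** The article gives no operating characteristics for the F-test. Its only power figure is the paired t-test in Statistical considerations (10% reduction, SD 20%, alpha 0.05, power 80%, N = 33). The normal approximation is (20 × (1.960 + 0.842) / 10)² = 31.4, so 32. The exact two-sided t-test has 79.5% power at 33 and 80.8% at 34, and with 30 patients detects 10.6% (10.5% stated). That figure stands and does not depend on the F-test.

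**Inputs.** From the article: 30 datasets, five follow-up GFR values each, a one-parameter linear comparator. Assumed, because the article gives none of them: slopes of 0, 0.5, 1 and 2 per unit of mean dose, residual SD 10, the patients' dose distributions, and stand-in rival models. The linear model is true throughout, and each setting has 1,500 runs.

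**Statistic.** F = [(RSS_line − RSS_rival) / (p − 1)] / [RSS_rival / (n − p)], referred to the upper 5% point of F(p − 1, n − p), where p is the rival's number of parameters.

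**Step 1: one value per patient, n = 30, independent errors.**

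| Rival model | Rejection at nominal 5% | Runs with F < 0 |
|---|---|---|
| Line plus quadratic (nested control, p = 2) | 4.2% to 5.0% | 0% |
| Dose threshold and amplitude (not nested, p = 2) | 1.0% to 9.1% | 0.5% to 92% |
| Sigmoid local response fitted on a grid (p = 3) | 0% to 2.7% | 1% to 50% |

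The control shows that the test works when its condition holds. For the threshold model the level moves with the unknown slope: 1.0%, 9.1%, 8.2% and 2.6% at slopes 0, 0.5, 1 and 2. Part of the negative share for the sigmoid reflects its limited parameter grid.

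A second simulation, with other sigmoids (one GFR change each, 400 runs), gave negative F in 18% of runs with two parameters and 3% with three, with rejection about 4%.

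**Step 2: five values per patient treated as 150 independent residuals.**

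- Nested control, within-patient correlation 0.5: 26.8% to 27.7% rejection. With correlation 0: 4.9% to 5.5%.
- Threshold model (slopes 0 to 1), correlation 0.5: 17% to 43%. With correlation 0: 1.0% to 7.9%.
- Three-parameter sigmoid, between-patient SD 12% and within-patient SD 9%: 35% (200 runs). The implied correlation is 12² / (12² + 9²) = 144/225 = 0.64.

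**Step 3: check of step 2 by hand.** Dose is fixed within a patient, so pooling five values inflates the numerator by about 1 + (5 − 1) × 0.5 = 3. For one added parameter the critical value of F(1, 148) is 3.91, and 3.91 / 3 = 1.30. The chance that F(1, 148) exceeds 1.30 is about 26%, in line with the simulated 27%. At correlation 0.64 the factor is 3.56, the threshold becomes 3.91 / 3.56 = 1.10, and the chance is about 30%. This inflation comes from ignored correlation and arises even when the models are nested.

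**The case against.** **Non-nesting is an inference.** A reader might conclude that the linear model is definitely not contained in the rivals. The article gives no equations, the list is open, and some forms could approach a line as a limit, for example a sigmoid with a very large half-effect dose. This stands: the supportable statement is that nesting is not shown and is unlikely. The limiting case does not rescue the test, because the line is reached only as a parameter runs to infinity, where standard F theory does not apply.

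**The F-test is not the sole criterion, nor the test of hypothesis 2.** Confidence intervals are named in the same sentence, and prediction is assigned to the 20/10 patient split. This stands. However, the intervals do not compare models and the split predicts SPECT signal, so the comparison of the GFR models with a line still rests on the F-test.

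**With one value per patient the harm is modest.** A negative F would be read as no improvement over the line, which is correct when the line is true, and rejection was mostly below 5%. This stands. A reader might infer from the 35% that non-nesting makes the complex model win wrongly. It does not show that, since most of that figure is due to pooling correlated visits, and the article does not say that visits are pooled.

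**An undefined test through equal parameter counts.** Zero numerator degrees of freedom would need a rival with one parameter. The article speaks of model parameters in the plural and gives no counts, so this is speculation.

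**Conclusion.** The concern holds in a limited form. The article commits to an F-test whose two conditions, nesting and independent residuals, it does not establish for the models named.

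Without nesting, the statistic can be negative and its level depends on unknown quantities: 1% to 9% at nominal 5% for the stand-in threshold model. If repeated GFR values are pooled without a within-patient term, false preference for the larger model is roughly 27% to 35% at assumed correlations of 0.5 to 0.64. The 27% comes from a nested model and the 35% from a sigmoid. These sizes rest on stand-in models and assumed slopes, SDs and correlations, so they show direction and order of magnitude, not the error rate of the planned analysis.

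A reader might infer that this is a must-fix defect at the heart of the study. The documents do not support that. It concerns one model-comparison step in an observational study and leaves the sample size, the mixed model of item i and the NTCP/EUD fits untouched. It is a moderate issue.

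**What to change.** In item iii, replace the F-test as the general comparison with one that does not need nesting. Any of these would serve:

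- AICc from the fitted likelihoods.
- A Vuong test, or a parametric-bootstrap test that takes whole patients as the unit.
- Patient-level cross-validated prediction of GFR, leaving out all visits of a patient together.

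Include a patient random effect for repeated GFR in both the spatio-temporal and the linear model, as item i does for SPECT signal. Keep the F-test only for pairs for which the plan shows that the linear model is a special case. The parameter confidence intervals can stay as a description of precision.

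The cost is revised analysis wording and modest extra computing. The models are already to be fitted by maximum likelihood, and no further data or patients are needed.
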